## Abstract

**Background:**

Lifestyle modifications are considered the most effective means of delaying or preventing the development of type 2 diabetes (T2DM). To contain the growing population of T2DM, it is critical to clarify effective and efficient settings for intervention and modalities for intervention delivery with a wide population reach.

The Japan Diabetes Outcome Intervention Trial-1 (J-DOIT1) is a cluster randomized controlled trial to test whether goal-focused lifestyle coaching delivered by telephone can prevent the development of T2DM in high-risk individuals in a real-world setting. This paper describes the study design and recruitment of the study subjects.

**Methods:**

For the recruitment of study subjects and their follow-up annually over 3 years, we employed health checkups conducted annually at communities and worksites. Health care divisions recruited from communities and companies across Japan formed groups as a cluster randomization unit. Candidates for the study, aged 20-65 years with fasting plasma glucose (FPG) of 5.6-6.9 mmol/l, were recruited from each group using health checkups results in 2006. Goal-focused lifestyle support is delivered by healthcare providers via telephone over a one-year period. Study subjects will be followed-up for three years by annual health checkups. Primary outcome is the development of diabetes defined as FPG≥7.0 mmol/l on annual health checkup or based on self-report, which is confirmed by referring to medical cards.

**Results:**

Forty-three groups (clusters), formed from 17 health care divisions, were randomly assigned to an intervention arm (22 groups) or control arm (21 clusters) between March 2007 and February 2008. A total of 2840 participants, 1336 from the intervention and 1504 from the control arm, were recruited. Consent rate was about 20%, with no difference between the intervention and control arms. There were no differences in cluster size and characteristics of cluster between the groups. There were no differences in individual characteristics between the study arms.

**Conclusion:**

We have launched J-DOIT1, a nation-wide trial to prevent the development of T2DM in high-risk individuals using telephone-delivered intervention. This trial is expected to contribute to evidence-based real-world preventive practices.

**Trial registration:**

UMIN000000662.

## Background

Type 2 diabetes mellitus (T2DM) is rapidly becoming one of the major health issues of the 21^st^ century [1,2]. A recent survey performed by the Ministry of Health, Labour and Welfare has projected that approximately 8.9 million people have diabetes and another 13.2 million people are at high risk for diabetes in Japan [3,4]. There is an urgent need for effective strategies to combat this pandemic. The Finnish Diabetes Prevention Study (DPS) [5] and US Diabetes Prevention Program (DPP) [6] both clearly showed that intensive lifestyle intervention can prevent or delay the development of T2DM in a high-risk population. Thus, lifestyle modifications are considered the most effective means of delaying or preventing the development of T2DM [7,8]. The DPP and DPS interventions have been translated into church [9], weight loss clinic [10], YMCA [11], primary care [12], and community [13] settings. However, translating the findings of clinical research, such as the DPS and DPP, into a real-world practice [14] on a large-scale still remains to be addressed. Japan has adopted the universal medical care insurance system, where all the people are insured by one of the public medical insurance systems [15,16]. In 2003 the Health Promotion Law was enforced aiming at preventing lifestyle-related diseases including T2DM. Now it has become mandatory for all Japanese adults to undergo health checkups provided by public medical care insurance at least once a year. There are two main types of statutory health checkup programs; 1) workplace health checkup programs managed by employers (companies setting), and 2) community health checkup programs managed by municipalities (communities setting) for self-employed, unemployed and retired individuals. People are registered at health care divisions in their workplaces or communities, and through the health care divisions, health checkups are provided. Health checkups are becoming part of routine health care. As a whole about 50% of adults undergo health check-ups annually. A large number of high-risk subjects for diabetes are identified every year through these health checkups. It is questionable, however, to what extent annual health checkups contribute toward overcoming the pandemic of diabetes. There is a big gap between identifying high risk subjects and preventing diabetes in the real world. One of the reasons for this may be a lack of evidence-based effective and efficient prevention programs which are easily accessible. The Japan Diabetes Outcome intervention Trial-1 (J-DOIT1) is a nation-wide, cluster randomized controlled trial [17], aiming to establish effective and efficient programs to prevent the development of T2DM in high-risk individuals through lifestyle modifications. The cluster randomization design has the advantages of administrative convenience, ease of obtaining the cooperation of investigators, enhancement of subject compliance, and avoidance of treatment contamination [18]. Health care divisions recruited from communities and companies across the country formed groups as a cluster randomization unit. The data of annual health checkups obtained from each group are utilized for identifying high-risk individuals and follow-up. This paper presents the study protocol in detail, including the rationale and the recruitment results. As a national project, this information should be widely referred to and shared by researchers and practitioners in preventive medicine.

## Methods

This study has been approved by the Ethical Committee of the Japan Foundation for the Promotion of International Medical Research Cooperation (National Center for Global Health and Medicine, Tokyo, Japan).

### Study design

The present study is a cluster randomized controlled trial [19,20] aimed at involving Japanese men and women, aged 20-65 years, at high risk for developing T2DM. For the recruitment of study subjects and their follow-up, we employ health checkups conducted annually by health care divisions at communities and worksites. A total of 17 health care divisions were enrolled across the country. Large health care divisions, with a large number of examinees and branches covering different areas, were divided into groups. A total of 43 groups were thus formed from 17 health care divisions, with each group having approximately 1,000-6,000 annual health checkup examinees. For the cluster randomization, these groups were randomly allocated to either an intervention or a control arm. Using the 2006 health checkup data obtained from each cluster, lifestyle support centers sent a program kit to the candidates who met the eligibility criteria and invited them to participate in the study. The kit included an explanation about the study’s aims and protocol, a consent form, and a questionnaire regarding lifestyle and health status. Those who consented to participate and completed the questionnaire were registered as study participants at lifestyle support centers, after their eligibility was checked based on their self-reported health status. Subjects in the intervention arm will receive non-face-to-face intervention via telephone or mobile-phone over the course of one year. Subjects in control arm will receive no such intervention. The progression to diabetes will be monitored by an annual health checkup and questionnaire over three years. All data for the study are collected at the lifestyle support centers and sent to the data management center in a de-identified form.

### Recruitment of health care divisions

By advertising on the internet or by direct contact, we invited health care divisions at communities and companies to participate in the study. The inclusion criteria for the participating health care division were; 1) it conducts health checkups according to guidelines by the Health Promotion Law, 2) as a rule it has 2,000 or more examinees annually, 3) it can provide the study group with health checkups data every year starting from 2006, and 4) it can conduct lifestyle survey every year using a questionnaire prepared by the study team. Health care divisions, in which study team members are directly involved as industrial physicians, were excluded. Seventeen health care divisions, widely distributed throughout the country, agreed to participate in the study. Among them 14 health care divisions belonged to companies, 2 to municipalities, and 1 was a mixture of small-sized companies and municipalities. They were all approved by the steering committee. A large health care division, covering many distant areas, was divided into groups. This process was done by the health care division itself mainly based on the area and number of examinees. A total of 43 groups were thus formed from 17 health care divisions. The number of groups formed in each health care division ranged from 1 to 10. Each group included 700 to 6,000 annual examinees. Some groups that were small were pooled with others. Using the results of health checkups in 2006, candidates who met inclusion criteria (described later) were identified in each group.

### Randomization

For cluster randomization, the groups were randomly allocated to either an intervention (n=22) or a control (n=21) arm. Randomization was performed 3 times according to 3 recruitment periods (March to April, May to June, and July to August in 2007). When two or more groups were made from one health care division, they were allocated to each of the arms within the health care division. Some small groups were pooled with others. Allocation was carried out using stratified randomization with seven strata of companies or communities in the first period, five strata in the second period, and three strata in the third period. A randomization list was prepared by an independent statistician using the SAS PLAN procedure with seed = 4989. This procedure was conducted using SAS version 9.1 (SAS Inc., Cary, NC, USA). Simple randomization was performed with 2 levels of treatment. The groups were notified of their allocation status before study subjects were recruited. The subjects were notified of their allocation status when they were recruited.

### Health checkups

Guidelines for health check implementation were announced in 2004 based on the Health Promotion Law. In 2006 mandatory items to be checked included 1) anamnesis of past history including history of medication and smoking, 2) subjective and objective symptoms, 3) body height and weight, 4) Body Mass Index (BMI), calculated as body weight (kg) divided by square of body height (m^2^), 5) blood pressure, 6) serum alanine aminotransferase, asparate aminotransferase and gamma glutamyltranspeptidase, 7) serum triglycerides, HDL cholesterol and LDL cholesterol, 8) fasting plasma glucose, and 9) urinalysis. At health checkup sites anthropometric measurements were done by public health nurses or industrial nurses. Height was measured in the standing position by public health nurses or industrial nurses. Weight was measured without shoes or heavy clothes to the nearest 0.1 kg using standard calibrated scales. Systolic and diastolic blood pressure values were measured in the sitting position [21]. Blood was withdrawn after 8 hours of fasting and analyzed with standard methods in clinical laboratories under the nationally certified laboratory management system. If blood was withdrawn from people who had not fasted, plasma glucose data was treated as casual plasma glucose and triglycerides values were omitted from the analysis. We did not perform any additional tests for this study.

### Inclusion and exclusion criteria for study subjects

Using the 2006 year health checkups data, candidates who met the inclusion criteria were identified in each cluster. Inclusion criteria included an age of 20-65 years and impaired fasting glucose (IFG) defined as a fasting plasma glucose concentration (FPG) of 100-125 mg/dL (5.6-6.9 mmol/L). In the 2006 year health checkups, however, blood sampling was not always done in the fasting state. In those individuals where the FPG was not available, plasma glucose concentrations (casual plasma glucose, CPG) of 118-143 mg/dL (6.6-7.9 mmol/L) [22,23] were considered eligible. A CPG ≥11.1 mmol/l (200 mg/dl) indicates diabetic type of glucose tolerance according to the report of the committee on the classification and diagnostic criteria of diabetes mellitus [24,25]. A CPG is also used as the risk assessment for cardiovascular disease in Japan [26]. Exclusion criteria included diagnosed diabetes, a previous history of diabetes taking anti-diabetic agents, a HbA1c of ≥ 6.5% [27]. Women with a history of gestational diabetes could be enrolled. Physical or medical conditions that do not allow exercise, pregnancy or possible pregnancy, evidence for of type 1 diabetes mellitus, liver cirrhosis or chronic viral hepatitis (type B or type C), and use of a cardiac pacemaker were also included as exclusion criteria. We also excluded those who had already participated in other lifestyle modification programs and those who could not obtain the approval from their doctors.

### Enrollment of the study subject

We outsourced some parts of the study works to three existing private companies (Tokio Marine & Nichido Medical Service Co., Ltd., National Education Association, INC. VISIT HEALTH Co., Ltd., and Meiji Yasuda System Technology Co., Ltd., Japan). They were all practicing healthcare services. They participate in this study as a lifestyle support center, which managed the recruitment and enrollment of study subjects and the lifestyle intervention. The lifestyle support center sent a program kit by mail to the eligible subjects in each cluster, inviting them to participate in the study. The kit included an explanation about the study’s aims and protocol, a consent form, and a questionnaire regarding lifestyle and health status. Those who consented to participate and completed the questionnaire were enrolled as study participants at the lifestyle support center, after their eligibility was checked based on their self-reported present and past health conditions and, when available, based on information from physicians in the health care divisions.

### Characteristics of study subjects

As mentioned above, using a questionnaire, subjects in both the intervention and control arms were asked about their lifestyle (diet, exercise habits, and smoking history) and present and past health conditions. They were categorized into following groups by their BMI, based on the WHO Western Pacific Regional Office (WPRO) criteria; <18.5 as “Underweight”, 18.5 to 22.9 as “Normal”, 23.0 to 24.9 as “Overweight”, 25.0 to 29.9 as “Obese I”, and ≥30.0 as “Obese II” [28,29]. To define the Metabolic Syndrome in this study we used the modified criteria of the third report of the National Cholesterol Education Program Expert Panel on Detection, Evaluation, and Treatment of High Cholesterol in Adults (NCEP/ATPIII) [30,31]. When three or more of the following components were present in an individual, the individual was judged to have the Metabolic Syndrome: 1) serum triglycerides ≥150 mg/dL [≥ 1.69 mmol/L];, 2) HDL-cholesterol <40 mg/dL [< 1.04 mmol/L] for men and <50 mg/dL [< 1.29 mmol/L] for women, 3) fasting plasma glucose ≥100 mg/dL [≥ 5.6 mmol/L], 4) blood pressure ≥130/85 mmHg, or use of blood pressure lowering agents, and 5) a BMI of ≥25 kg/m^2^[32]. In 2006, when the baseline data were obtained, waist size was not measured in the majority of the health checkup sites. Therefore, BMI was substituted for waist circumference.

### Goals for lifestyle changes

The goals for lifestyle change are set for each subject from the following four points; 1) habitual exercise (10,000 steps or more per day or 60 min or more per week of accumulated moderate levels of exercise), 2) achievement and maintenance of an appropriate body weight (a 5% reduction in body weight in subjects with a BMI of ≥25 kg/m^2^ or a 3% reduction in subjects with a BMI of 23.0-24.9 kg/m^2^), 3) habitual intake of dietary fiber (five or more dishes of vegetables per day or 350 g or more of vegetables per day ), and 4) restrictions on alcohol intake (1 “go” (180 ml) or less per day in terms of Japanese sake. 1 “go” of Japanese sake contains 23 g of ethanol [33]).

### Lifestyle intervention

After setting goals, the intervention and control arms will receive different treatments. For subjects in the control arm, a weight scale (HBF-354 IT-2; Omron Healthcare Co., Ltd., Japan) and a pedometer (HJ-710 IT; Omron Healthcare Co., Ltd., Japan) with a storage function are provided. They will periodically receive newsletters from the lifestyle support center, which run health-related information and messages to encourage them to undergo a health checkup regularly. These are done to minimize the potential for greater attrition from subjects in the control arm. For the subjects in the intervention arm, in addition to the services provided to the control arm, telephone-delivered lifestyle support will be provided over a one-year period through one of the three lifestyle support centers. In addition to phone calls, written information delivered by mail is also used. Subjects monitor achievement of their own personal action plan. They are encouraged to measure body weight and the number of footsteps every day and send the accumulated data to the lifestyle support center monthly via a transmitter (DC-100; JMS Co., Ltd., Japan). The staff will monitor the achievement of subject’s goals regularly and give advice by phone or mail (Figure 1). As mentioned before the intervention is outsourced to private companies. Because the sample size is large, we use three companies. The National Education Association, INC. VISIT HEALTH Co., Ltd., Ltd., Meiji Yasuda System Technology Co., Ltd., and Tokio Marine & Nichido Medical Service Co., Japan will manage 16, 18 and 9 groups, respectively. All study subjects in each group will be managed by the same company. We do not standardize the intervention program. Each company uses its own intervention schedule approved by the study group (Table 1). The intervention is standardized within each company. Public health nurses and registered dieticians employed by the lifestyle support centers have college degree and at least 5 years work experience of the intervention. In addition, we will hold educational sessions on diabetes and its prevention for them and training sessions to improve their skills of telephone counseling with motivational interviewing. As shown in the Table 1, there are considerable differences in the quantity of services among the companies. Participants will receive phone calls at least 3 times, and at most 10 times, over one year with the length of each call being between 15-30 minutes.

**Figure 1 F1:**
[figure not shown]
Telephone-delivered lifestyle modification support model: theory matrix.

**Table 1 T1:** Schedules of telephone counseling of the three lifestyle support centers

	**National Education Association INC. VISIT HEALTH**	**Meiji Yasuda System Technology**	**Tokio Marine & Nichido Medical Service**
Introduction and welcome call	In Week 1	In Month 2	In Month 3
Support calls	In Months 2, 3, 4, 7, and 10.	In Months 3, 4, 5, 6, 7, 8, 9, 10, and 11.	In Months 7 and 12
Advice sheets by mail	No	Monthly, during Month 2-12	Monthly, during Month 2-12
Feedback by graph (body weight and footsteps)	Monthly	Monthly	Monthly
The number of groups in the control/intervention arm	8/8	8/7	4/5
The number of subjects in the control	595/722	413/484	328/298

Data are n.

### Follow-up and outcome

Participants will be followed up over a three- year period using data from an annual health checkup and a questionnaire regarding health and lifestyle. The questionnaires are mailed out to the participants from the lifestyle support center with self-addressed envelopes. If a completed questionnaire is not sent back to the lifestyle support center within two weeks, the lifestyle support center will contact the participant first by mail and then by telephone. We made a manual for this process. The primary outcome is the development of diabetes in participants whose FPG concentration is 100-125 mg/dL (5.6-6.9 mmol/L) at baseline. The development of diabetes is defined as; #1) a rise in FPG to a level equal to or greater than 126 mg/dL (7.0 mmol/L) as revealed in the follow-up annual health checkup, and #2) a diagnosis of diabetes or use of anti-diabetic drugs as reported in the annual questionnaire with confirmation by referring to medical records. Other outcomes are changes in body weight, BMI, plasma glucose, blood pressure, serum lipids, HbA1c, the percentage of subjects with the Metabolic Syndrome, lifestyle, and the development of cardiovascular diseases.

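### Diagnosed or drug-treated diabetes enters the primary endpoint only through the mailed questionnaire, although the check-up also takes a medication history; a treated non-responder with FPG below 126 mg/dL is not counted as an event

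*Protocol article*

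**What the plan says.** The Follow-up and outcome section of the protocol article defines the primary event by two criteria, read here as alternatives, as the abstract words them.

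- Criterion #1 is taken from the check-up: "a rise in FPG to a level equal to or greater than 126 mg/dL (7.0 mmol/L) as revealed in the follow-up annual health checkup".
- Criterion #2 is "a diagnosis of diabetes or use of anti-diabetic drugs as reported in the annual questionnaire with confirmation by referring to medical records".

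The same section describes how the questionnaire travels: "The questionnaires are mailed out to the participants from the lifestyle support center with self-addressed envelopes". If it is not back within two weeks, "the lifestyle support center will contact the participant first by mail and then by telephone", following a manual. The Limitations section again names only check-up FPG and a questionnaire as the follow-up sources. The abstract is looser: "FPG≥7.0 mmol/l on annual health checkup or based on self-report, which is confirmed by referring to medical cards".

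Two other places bear on the point. The Health checkups section gives, as the first mandatory item in 2006, "anamnesis of past history including history of medication and smoking". Recruitment of health care divisions makes it a condition of entry that a division confirms "it can provide the study group with health checkups data every year starting from 2006".

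**The concern.** Once a participant takes anti-diabetic drugs, FPG may fall below 126 mg/dL because of the treatment, so criterion #1 cannot be relied on to find the case. Criterion #2 is meant to cover this gap, but it works only if a mailed form comes back. Take two participants in the same state: diagnosed in clinic in year 2, on drugs, check-up FPG 112 mg/dL. One returns the questionnaire, the diagnosis is confirmed in the records, and the event counts. The other returns nothing. Even if the drug is noted in the check-up history, the definition gives no route for it to count.

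At stake are some lost or late primary events and, if return differs by arm, a distorted comparison. A difference by arm is plausible. Participants and staff are unblinded, and the lifestyle support centers that mail and chase the questionnaires also coach the intervention arm by telephone (3 to 10 calls) but not the control arm. Enrolment was 2,840 against a target of 3,426, so there is little reason to give events away.

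**Working it through.** **1. The plan's own figures (reproduced, not contested).** Inputs from Sample size: 4% a year in control, 50% reduction, two-sided 5%, 90% power, 3 years. The Freedman formula gives (1.96 + 1.28)² × [(1 + 0.5)/(1 − 0.5)]² ≈ 95 events. The 3-year risks are 1 − 0.96³ and 1 − 0.98³, with mean 0.0870, so N = 95/0.0870 ≈ 1,092. With exponential rates (mean 0.0857) N is about 1,110. Both agree with the stated 1,100. Then 1 + 59 × 0.02 = 2.18; 1,100 × 2.18 = 2,398; 2,398/0.7 ≈ 3,426.

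**2. Expected events in the enrolled sample, with 30% loss.**
- Control: 1,504 × 0.7 × (1 − e^−0.12) = 119.1
- Intervention: 1,336 × 0.7 × (1 − e^−0.06) = 54.5
- Total: about 174

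**3. Assumptions, because the documents give no figures.**
- s = share of events that only diagnosis or treatment reveals, with later FPG staying below 126 mg/dL: 20-40%.
- q = yearly questionnaire non-return after reminders, among check-up attenders: 10-30%. Half of it is persistent (the person never returns a form) and half is independent from year to year.
- Onsets are spread evenly over the three years. A treated case counts at its first returned questionnaire, and otherwise stays event-free.

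**4. Formula.** Let a = q/2 and b = (q/2)/(1 − q/2). The share of treated cases never captured is L = a + (1 − a)(b + b² + b³)/3. Lost events = s × L. Events captured a year or more late = s × (q − L).

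| q | L | lost, s = 20% | lost, s = 30% | lost, s = 40% |
|---|---|---|---|---|
| 10% | 0.068 | 1.4% | 2.0% | 2.7% |
| 20% | 0.138 | 2.8% | 4.1% | 5.5% |
| 30% | 0.210 | 4.2% | 6.3% | 8.4% |

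A simulation of the same model gives 1.2-8.2% over this grid. At s = 30% and q = 20%, about 4% of 174, or 7 events, are lost and 0.3 × (0.20 − 0.138) ≈ 2% are late. Across the grid, 0.6-4% are late. With no late capture the loss is simply s × q; widening s to 10-50% then gives 1-15%.

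**5. Equal non-return in both arms.** Both event probabilities shrink by the same factor. With the compound risks above, the hazard ratio is 0.495 with nothing missed and 0.495-0.497 over the 1-15% range. Power, with 2,840 enrolled, 30% loss and design effect 2.18, is about 0.88 with nothing missed, 0.85 with 7.5% missed and 0.82 with 15% missed.

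**6. Unequal non-return.** The hazard ratio is multiplied by about (1 − sL in intervention)/(1 − sL in control). For q = 15%, L = 0.102.
- Control 30%, intervention 15%: from 0.980/0.958 = 1.02 (s = 20%) to 0.959/0.916 = 1.05 (s = 40%).
- The reverse: 0.98 to 0.96.
- More extreme, 30% against 10%, s = 10-50%, no late capture: a true ratio of 1 appears as 1.02-1.13 if control under-returns and 0.98-0.89 if intervention does.

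**The case against.** Several objections are fair.

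- **The check-up drug history may not be in hand.** A reader might infer that the data identifying these cases already sit in the study database. The documents do not show this. The Health checkups list describes what was mandatory in 2006. The opening of the Discussion speaks only of biochemical and anthropometric data from check-up sites. Limitations says that information on some lipid-affecting drugs is lacking. The metabolic syndrome definition uses "blood pressure ≥130/85 mmHg, or use of blood pressure lowering agents" but names no source for the drug item. This stands: availability has to be verified. It does not remove the point, because Limitations does not mention anti-diabetic drugs and a coarse flag suffices when records are checked afterwards.
- **Such a participant need not be scored diabetes-free.** A reader might infer that the non-responder stays in the risk set as diabetes-free. The text does not say so. Statistical analyses omits cases with missing data, and Dropout and discontinuance includes people who have lost contact. Either could apply. Under none of these readings is the case counted as an event.
- **Reminders exist.** Mail and then telephone contact lowers non-return, and a later form can recover a case. Neither guarantees capture, and recovery may be late.
- **The abstract's wording is wider.** Its reference to self-report does not exclude a check-up history. The detailed Methods definition is narrower, and it is the one an analyst would apply.
- **Check-up history is also self-report.** True. It is nevertheless a second route, and the existing record confirmation would cover it.

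**Conclusion.** The point holds in limited form. As defined, criterion #2 has a single trigger, and a treated participant with FPG below 126 mg/dL who never returns a questionnaire is not counted as an event. How that person is then classified is not stated.

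The size rests wholly on assumed inputs: about 1-8% of events lost for s of 20-40% and q of 10-30%, and up to 15% under wider assumptions without late capture. If treated cases often still show FPG of 126 mg/dL or more, the loss is smaller. Equal non-return costs a little power and leaves the hazard ratio nearly unchanged. Unequal non-return moves it by a few per cent, up to roughly 11-13% in the extreme case. A reader might infer a bias towards no effect from the heavier contact with the intervention arm. No return rates by arm are given, so the direction is open.

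This is a minor, inexpensive improvement to event capture. No stated figure is wrong.

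**What to change.** Extend criterion #2 so that a diagnosis or anti-diabetic drug use can be triggered either by the annual questionnaire or, where the supplied check-up data contain it, by the past or medication history taken at the annual check-up. Keep medical-record confirmation for both triggers. Apply the rule identically in both arms, and report by arm how many events enter through FPG, questionnaire and check-up history.

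Cost: one sentence in the endpoint definition, extraction of a field where it exists, and a few more record confirmations. No new test or visit is needed. Downside: the history may be coarse, or not supplied by every division, so its availability in the follow-up years must be checked before the route is relied on.
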